In many countries, cytisinicline is prescribed as a single 25-day course. Studies to date show that the current 25-day cytisinicline regimen is better tolerated and has fewer side effects [20]. However, there is a patient profile in whom this 25-day cytisinicline regimen is not sufficient to control cravings and withdrawal symptoms, increasing the likelihood of relapse, reducing the chances of quitting smoking, and discouraging these smokers from making another serious quit attempt with an effective drug. Recent data from Spain on experience in routine clinical practice with a 25-day cytisinicline regimen show a high rate of relapse after completing treatment. Twenty percent of smokers treated with cytisinicline at this regimen resume smoking from the end of treatment until 2 months after follow-up [25]. Establishing an optimization strategy based on prolonging treatment could increase the drug’s efficacy without being associated with a greater number of side effects, generating a favorable economic impact by increasing the number of smokers who permanently quit. We hypothesize that there is a correlation between increasing the duration of cytisinicline and its efficacy, without being associated with a greater number of adverse events/side effects.

Therefore, we aim to compare the efficacy, safety, and economic impact of this treatment regimen used in routine clinical practice in Spain versus 2 proposed extended treatment regimens (double and triple duration). Different drugs are not compared, but rather 3 different treatment regimens (25, 50, and 75 days) of the same drug (cytisinicline), one of which is the treatment regimen used in daily clinical practice.

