### Specific Outcomes Efficacy

Different outcomes will be used to measure the efficacy of cytisine in each arm of the clinical trial.

The sustained abstinence rate will be determined in each of the three treatment arms at 6 and 12 months, based on carbon monoxide co-oximetry results in ppm. The correlation between the sustained abstinence rate in each of the three arms studied at 6 and 12 months, based on co-oximetry results, and the self-reported abstinence at 6 and 12 months will be calculated.

Additionally, point abstinence will be analyzed every 7 days in each of the 3 arms studied, based on the results obtained in the CO tests.

The percentage increase in abstinence rates will be compared with the increase in the duration of cytisinicline use. The number needed to quit smoking for one patient in each treatment group will also be calculated.

Interval abstinence will also be determined in this clinical trial. The abstinence rate will be analyzed from Day 25 to Day 50 in all 3 study groups and from Day 25 to Day 75 in all 3 study arms. The abstinence rate will also be determined from Day 25 (usual arm), Day 50 (extended arm 1), and Day 75 (extended arm 2) up to 6 and 12 months.

Relapse rates will be analyzed in each treatment arm. The frequency and percentage of relapses will be determined in those who quit smoking from Day 25 (usual arm), Day 50 (extended arm 1), and Day 75 (extended arm 2) up to 6 and 12 months in all 3 arms.

Craving and withdrawal symptoms will be assessed during the clinical trial. The mean Minnesota Nicotine Withdrawal Scale (MNWS) score and the mean craving score will be calculated at the initial in-person visit in all 3 arms, and their change from this visit will be measured on days 25, 50, and 75 in all 3 study arms.

Predictors of continued abstinence at 6 and 12 months of treatment and of relapse (clinical, anthropometric, demographic, and smoking-related variables) will be determined in all study arms.

Quality of life in each group will be calculated using the EQ-5D-5L scale score at baseline, 50 days, 90 days, 6 months, and 1 year.

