### Schedule of Participants

Table 3 and Figure 1 show the screening visit, follow-up visits (face-to-face and telephone), tests and quizzes to be carried out at each of the visits, and the interventions.

**Table 3 table3:** Visiting calendar. The screening visit, follow-up visits (face-to-face and telephone), tests and quizzes to be carried out at each of the visits, as well as the intervention.

Number, day, and type of visit		Visit 1 (day 1; in person)		Visit 2 (day 7; in person)		Visit 3 (day 14; telephone)		Visit 4 (day 21; in person)		Visit 5 (day 25; telephone)		Visit 6 (day 50; telephone)		Visit 7 (day 75; telephone)		Visit 8 (day 90; in person)		Visit 9 (day 120; in person)		Visit 10 (day 150; in person)		Visit 11 (week 24; in person)		Visit 12 (week 36; telephone)		Visit 13 (week 48; in person)		Visit 14 (week 52; in person)			

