### Efficacy Analysis

To determine the main objective of the work, the efficacy variable will be constructed as a dichotomous variable, resulting from an algorithm that will be constructed for this purpose once all the data from the study have been obtained. To study the causality between efficacy and treatment prolongation, a multivariate logistic regression will be constructed. To determine candidate variables, candidate variables will first be tested in a univariate regression. Those variables whose statistical significance has a *P* value of <.20 will become part of a multivariate model. The model that best explains causality will be determined using a measure of relative statistical model quality, the Akaike information criterion. The risk measure to be calculated is the relative risk with its 95% CI. Interim follow-up assessments will be analyzed using a survival analysis to determine the duration of abstinence after the smoking cessation date.

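### Two supplementary outcomes, interval abstinence and relapse to 6 and 12 months, start at day 25, 50 or 75 by arm but end on the same date, which favours the longer regimens even if duration has no effect

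*Protocol article*

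**What the plan says.** Under Specific Outcomes Efficacy, the article defines an abstinence rate that runs "from Day 25 (usual arm), Day 50 (extended arm 1), and Day 75 (extended arm 2) up to 6 and 12 months". The relapse outcome uses the same arm-specific starts: "The frequency and percentage of relapses will be determined in those who quit smoking", counted from those days to 6 and 12 months. No allowance for the unequal lengths is described.

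Other efficacy analyses do not share this feature:
- The same section plans windows common to all arms: "The abstinence rate will be analyzed from Day 25 to Day 50 in all 3 study groups", and likewise days 25 to 75.
- Sustained abstinence at 6 and 12 months is listed first among the efficacy outcomes, with no starting day stated.
- Textbox 2 lists abstinence from day 25 to 6 months without arm-specific starts.
- The Efficacy Analysis section says: "Interim follow-up assessments will be analyzed using a survival analysis to determine the duration of abstinence after the smoking cessation date".

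The Methods part of the abstract says that differences among the three groups will be calculated for each outcome variable by univariate analysis. The Trial Design section states a superiority aim.

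**The concern.** Each arm's clock starts at its planned end of treatment, while the end is a fixed date after treatment start. This can favour arm C in three ways without any drug effect.

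1. Fewer days are counted in which a relapse can occur. There are also fewer contacts at which it can be recorded: Table 3 has six after day 25 up to week 24, five after day 50 and four after day 75.
2. Smoking or relapse between day 25 and day 50 or 75 counts against arm A but is ignored in B or C.
3. If the denominator is people abstinent at the start day, arm C's denominator has been filtered for 50 days longer than arm A's and so holds more stable quitters.

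All three push towards less relapse and more interval abstinence with longer treatment, which is what the trial hopes to show. A between-arm comparison on these windows could therefore be read as lasting benefit when it reflects where the clock was started.

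**Working it through.** **Inputs.** Start days 25, 50 and 75 come from Specific Outcomes Efficacy. End days come from Table 3: week 24 = 24 × 7 = day 168, and week 52 = 52 × 7 = day 364. The quit deadline is day 5 (Table 1). For calibration, the Background says 20% of treated smokers "resume smoking from the end of treatment until 2 months after follow-up". I take this as 20% of quitters in 60 days, which is an assumption. The article gives no figure for time at risk, so there is nothing of its own to reproduce.

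**Time at risk (end day minus start day).**
- Week 24: 168 − 25 = 143; 168 − 50 = 118; 168 − 75 = 93. Arm C has 93/143 = 65% of arm A's exposure.
- Week 52: 364 − 25 = 339; 364 − 50 = 314; 364 − 75 = 289. Arm C has 289/339 = 85%.

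**Case 1: duration has no effect.** All arms share one relapse curve from the day-5 quit date, S(t) = exp(−λ(t − 5)^k). Relapse among those abstinent at start day s, up to end day E, is 1 − S(E)/S(s). Setting 20% relapse between days 25 and 85 gives λ = −ln(0.8)/(80^k − 20^k). With k = 1 (constant hazard), λ = 0.2231/60 = 0.00372 per day, and to week 24:
- A: 1 − exp(−0.00372 × 143) = 41.2%
- B: 1 − exp(−0.00372 × 118) = 35.5%
- C: 1 − exp(−0.00372 × 93) = 29.2%

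**Case 2: relapse is only postponed.** Each arm has the same curve after its own end of treatment, so relapse is 1 − exp(−λ(E − s)^k) with λ = −ln(0.8)/60^k.

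Relapse in %, arms A / B / C; k is the Weibull shape (assumed), and a smaller k means a faster-falling hazard:

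| k | No effect, week 24 | No effect, week 52 | Postponed, week 24 | Postponed, week 52 |
|---|---|---|---|---|
| 1 | 41.2 / 35.5 / 29.2 | 71.7 / 68.9 / 65.9 | 41.2 / 35.5 / 29.2 | 71.7 / 68.9 / 65.9 |
| 0.5 | 33.9 / 26.1 / 19.7 | 51.4 / 45.7 / 41.0 | 29.1 / 26.9 / 24.3 | 41.2 / 40.0 / 38.7 |
| 0.3 | 31.6 / 22.9 / 16.6 | 44.9 / 37.9 / 32.9 | 25.1 / 23.9 / 22.5 | 31.3 / 30.7 / 30.1 |

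The no-effect A–C gap is 12.0 points (k = 1) to 14.2 (k = 0.5) at week 24, and 5.8 to 10.4 at week 52. At k = 0.3 it is about 15 and 12. The postponement gap runs from 12.0 points (week 24, k = 1) to 1.2 (week 52, k = 0.3).

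**A different denominator.** If all quitters are the denominator and relapses are counted only from the start day, the no-effect A–C gap is S(25) − S(75), whatever the end day. For k = 1 this is exp(−0.00372 × 20) − exp(−0.00372 × 70) = 0.928 − 0.771 = 15.8 points. For k = 0.5 (λ = 0.0499) it is 0.800 − 0.659 = 14.1 points. This reading does not remove the bias.

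**Interval abstinence in all randomised.** Here the advantage comes from participants who smoked before day 50 or 75 and then quit or quit again. The relapse model has no such people, so it gives the direction but no size.

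**With a common start at day 25.** Every arm has 143 days to week 24 and 339 to week 52. Under no effect with k = 1, all three arms then show 41.2% relapse to week 24.

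**The case against.** **Scope.** A reader might infer that the trial's main abstinence result is biased. The article does not support that. No start is given for sustained abstinence at 6 and 12 months, and the days 25–50 and 25–75 windows and the survival analysis from the cessation date use origins common to all arms. Only two supplementary outcomes are affected.

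**Postponement.** A reader might also infer that a common window would remove any advantage of merely delayed relapse. It would not. Suppose the same share is abstinent at each arm's end of treatment and the same constant hazard follows. Then 58.8% of that share in A and 70.8% in C are still abstinent at week 24 (100 − 41.2 and 100 − 29.2), whatever the origin. Only equal follow-up after treatment separates delay from prevention. What the arm-specific start adds is a difference when there is no effect at all. This objection stands, and the two cases are kept apart above.

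**Denominator and size.** The wording does not settle whether quitters means people abstinent at the start day, so it cannot be said that arm C contains only people who lasted 75 days. The 20% is stated for treated smokers, not clearly for quitters. Both points stand as limits on the size, not the direction.

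**Textbox 2.** It is tempting to call its day-25-to-6-month variable a contradiction. It may simply be an additional common-window variable, so clarification is enough.

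**Testing.** The section itself only says the rates will be determined and analysed, and details may sit in a plan not shown. An end-of-treatment relapse rate is also a reasonable clinical description. But the abstract announces group differences for each outcome variable, and the article does not leave these windows open: it fixes them, differently by arm.

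**Conclusion.** The point holds for interval abstinence and relapse among quitters to 6 and 12 months. The unequal time at risk follows directly from the stated days. In every relapse scenario tried, the longer regimen looks better.

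The size rests on assumed hazard shapes, the 20% taken as a share of quitters, and a denominator of those abstinent at the start day. On that basis, relapse would differ between A and C by about 12 to 14 points at week 24 and 6 to 10 at week 52 with no effect of duration (shapes 1 to 0.5; slightly more at 0.3). It would differ by about 1 to 12 points if relapse is only postponed. For interval abstinence in all randomised participants the direction is the same, but the size cannot be computed from the article. This should be corrected, but it does not by itself undermine the sustained-abstinence result.

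**What to change.** - Make between-arm comparisons of abstinence and relapse to weeks 24 and 52 from one origin common to all arms, in all randomised participants. Use either the quit date or day 25. Day 25 matches Textbox 2, and Table 1 gives all arms the same schedule up to that day. This removes the no-effect bias but not an advantage from postponement.
- To study relapse after stopping treatment, report it over an equal length of follow-up after each arm's planned end of treatment, for example about 90 days. Existing in-person visits come close: day 120 for A (120 − 25 = 95 days), day 150 for B (150 − 50 = 100) and week 24 for C (168 − 75 = 93). Label it descriptive, because it conditions on abstinence at an arm-specific day.
- Do not test arms on the unequal windows.
- State the relapse denominator, and say in Specific Outcomes Efficacy and Textbox 2 which day-25-to-6-month variable is used.

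The cost is outcome and analysis wording; the same visits and data serve. The downside for the investigators is that apparent relapse benefits of the longer arms may shrink.

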### Specific Outcomes (Safety)

The impact of morbidity and mortality in each treatment arm will be evaluated, as well as the percentage of side effects reported by participants, comparing their prevalence in each group throughout the study (1 year). The percentage of adverse effects at 25, 50, and 75 days will also be determined in participants, comparing their prevalence in each group.

Furthermore, the prevalence and severity of side effects for each regimen will be compared throughout the study (1 year).

Finally, the results of cardiac, hepatic, and renal variables will be compared between each group as indicators of treatment safety in each group at 25, 50, and 75 days of treatment and throughout the entire study period (1 year).

### Specific Outcomes (Economic Evaluation)

The economic analysis of 2 prolonged cytisinicline regimens vs a standard regimen will be performed by calculating their cost-effectiveness and cost-utility ratios. The effect of treatment adherence on the cost-effectiveness and cost-utility ratios of the considered therapeutic alternatives will also be evaluated.

The effect of the different predictors of sustained abstinence at 6 and 12 months (clinical, anthropometric, and demographic variables) will be evaluated in relation to cost-effectiveness and cost-utility in the three arms of the clinical trial.

The future effects (15, 30, and 50 years after smoking cessation) will be simulated in each of the treatment arms.

Finally, a budget impact model will be constructed to analyze the potential savings for the National Health System for each of the 3 therapeutic options proposed in this clinical trial.

### Schedule of Participants

Table 3 and Figure 1 show the screening visit, follow-up visits (face-to-face and telephone), tests and quizzes to be carried out at each of the visits, and the interventions.

**Table 3 table3:** Visiting calendar. The screening visit, follow-up visits (face-to-face and telephone), tests and quizzes to be carried out at each of the visits, as well as the intervention.

Number, day, and type of visit		Visit 1 (day 1; in person)		Visit 2 (day 7; in person)		Visit 3 (day 14; telephone)		Visit 4 (day 21; in person)		Visit 5 (day 25; telephone)		Visit 6 (day 50; telephone)		Visit 7 (day 75; telephone)		Visit 8 (day 90; in person)		Visit 9 (day 120; in person)		Visit 10 (day 150; in person)		Visit 11 (week 24; in person)		Visit 12 (week 36; telephone)		Visit 13 (week 48; in person)		Visit 14 (week 52; in person)			
**Variable registration**																															
	Sociodemographic		✓																												
	Anthropometric		✓																												
	Diagnostic		✓																												
	UISPM^a^ Test		✓																												
	Motivation		✓																												
	Reward		✓																												
	Spirometry		✓																												
	Advice		✓								✓		✓		✓		✓		✓		✓		✓		✓		✓		✓		
**Efficacy evaluation**																															
	Co-oximetry		✓		✓				✓								✓		✓		✓		✓				✓		✓		
	Statement		✓		✓		✓		✓		✓		✓		✓		✓		✓		✓		✓		✓		✓		✓		
Security assessment																															
Adverse events				✓		✓				✓		✓		✓																	
Quality of life assessment																															
EQ-5D		✓								✓		✓		✓				✓		✓		✓						✓			

^a^UISPM: Test of the Specialized Smoking Unit of the Community of Madrid.

### Data Collection Variables

With regard to patient information, a database will be designed specifically for this proposal. The medical and demographic data are as follows: age (years), sex (male/female), education level (no formal education, secondary education, or higher education) and social status (low, medium, or high). We establish cut-off points for the patient’s socioeconomic level according to the OECD (Organisation for Economic Co-operation and Development) based on the approximate monthly income level (less than €1000 (€1=US $1.16–$1.17) per month = low socioeconomic level, from €1000 to €3000 per month = medium socioeconomic level, and more than €3000 per month = high socioeconomic level). Questionnaires carried out in the SCUs are on current consumption, accumulated consumption, motivation, the quitting phase, and nicotine dependence. Smoking consumption characteristics are current number of cigarettes per day (categorized as ≥20 cigarettes per day), packs-year, previous quit attempts (previous attempts, previous attempts in the last year, previous attempts with drug treatment, and previous attempts with varenicline), and graded degree of smoking (mild, moderate, severe, or very severe) [27,28].

The different characteristics and clinical profiles of each smoker will be determined by the Test of the Specialized Smoking Unit of the Community of Madrid. It consists of 7 domains (stimulation, automaticity, sedation, psychological, gestural and social dependence, and automaticity). It allows for a more detailed identification of the smoker’s specific characteristics to optimize psychological and pharmacological treatment [27].

Nicotine dependence will be determined using the Fagerström test. It provides information about the patient’s physical dependence on nicotine. It is a questionnaire of 6 questions. A score of 7 or more indicates high nicotine dependence [29].

The reward associated with tobacco use will be measured in the clinical trial. We will use the reward test for this purpose. It indicates whether the smoker smokes for pleasure (positive reward), smokes to control withdrawal symptoms (negative reward), or both (mixed reward) [30].

The analysis of withdrawal symptoms in smokers will be performed using the MNWS. It allows for the detection of the intensity of withdrawal symptoms and their variation throughout the smoking cessation follow-up process [30].

Other qualities of the smoker, such as the degree of motivation and self-efficacy, will be evaluated by the Analogue Visual Scale. This scale numerically identifies a smoker’s level of motivation and self-efficacy to quit smoking. A score above 7 indicates high motivation and self-efficacy to quit smoking [27].

The EQ-5D scale will be used in this clinical trial to assess the quality of life of smokers and its changes during the smoking cessation process. This scale measures the health status of smokers using 5 dimensions, including mobility, self-care, activities of daily living, pain and discomfort, and anxiety and depression. Participants score from 0 to 100 in each domain [31].

The urge to smoke in this study will be analyzed using the Craving Rate Score. This scale assesses anxiety or intense desire to smoke at baseline and during follow-up. It is scored from 0 to 4 [32].

The additional tests that will be performed on smokers participating in this trial include electrocardiogram, carbon monoxide levels, complete blood count, and a biochemical profile that includes liver enzymes, electrolytes, and renal function tests. Co-oximetry allows for the objective identification of smoking status, as well as confirmation of abstinence at each participant visit. A participant is identified as a nonsmoker when their CO levels measured by co-oximetry are below 10 ppm (Textbox 2).

Efficacy and safety variables of cytisinicline.To analyze the efficacy of cytisinicline we used the following variables:Continuous abstinence rate at six months of treatmentEfficacy of the maintained cytisinicline regimens (50 and 75 days) compared to the usual 25-day regimen calculated every 7 daysIntervention interval effectivenessAbstinence rate between days 25 and 50Abstinence rate between days 25 and 75Abstinence rate between days 25 and 6 months calculated every 7 daysAnalysis of withdrawal syndromeMNWS score at each visitVariation in MNWS score between visitsMean MNWS score at each visitCraving AnalysisSRC score at each visitChange in SRC score at each visitAverage SRC score at each visitTo analyze the safety of cytisinicline, we used the following variables:Number and percentage of self-reported adverse events at the baseline visitNumber and percentage of self-reported adverse events on days 7, 15, 25, 50, and 75Number and percentage of mild, moderate, or severe adverse events on days 7, 15, 25, 50, and 75Number and percentage of serious adverse events on days 7, 15, 25, 50, and 75Number and percentage of the following adverse events: nausea, vomiting, constipation, abdominal distension, abdominal pain, epigastric pain, nightmares, insomnia, parasomnias, headache, and dizzinessPercentage of patients with electrocardiographic abnormalities at the initial visitPercentage of patients with electrocardiographic alterations at 25, 50, and 75 daysPercentage of patients with electrocardiographic alterations at 25, 50, and 75 daysPercentage of patients with abnormal liver enzyme levels at the baseline visitPercentage of patients with abnormal liver enzyme levels at 25, 50, and 75 daysPercentage of patients with abnormal electrolyte levels at the baseline visitPercentage of patients with abnormal electrolyte levels at 25, 50, and 75 daysPercentage of patients with abnormal renal function at the baseline visitPercentage of patients with abnormal renal function at 25, 50, and 75 days

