### Limitations

This study is not placebo-controlled; therefore, the effect of the intervention (extended cytisinicline treatment) cannot be accurately determined. The results of the intervention could be attributed not only to the drug but also to external factors. However, the use of a placebo could compromise the low level of intervention in this trial, according to regulatory authorities in Spain and the European Union. Furthermore, the synthesis of the placebo would hinder the feasibility of this study. Also, not including a placebo in the 25-day and 50-day treatment arms could provide results more aligned with routine clinical practice.

On the other hand, the efficacy and safety of different durations of cytisinicline treatment are not compared to other drugs for the treatment of nicotine dependence, such as varenicline or nicotine replacement therapy. This is because this is not the ultimate goal of this study. However, such a comparative analysis will be carried out in subsequent studies. The selected patient population consists of smokers attending SCUs with high nicotine dependence and associated comorbidities and does not represent the general smoking population. This selection bias may influence the greater efficacy of extended cytisinicline treatment. However, these are units of varying complexity, and smoking cessation can also be addressed in individuals with less nicotine dependence.

Because this is a low-intervention clinical trial, smokers older than 65 years and those with serious psychiatric or cardiovascular comorbidities are not included. Therefore, we cannot generate scientific evidence on extended treatment in these vulnerable populations.

Abstinence outcomes are objectively determined during in-person visits using co-oximetry. However, other more precise methods, such as cotinine determination in body fluids, are not used. Nevertheless, this test is accepted as a powerful marker for verifying abstinence, establishing a carbon monoxide (CO in ppm) cutoff point of less than 10 ppm [27]. Although different monitors may vary in their sensitivity to CO, combining this measurement with patient self-reporting improves the predictive capacity of co-oximetry.

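### The outcome text defines abstinence by CO below 10 ppm and only correlates self-report with it, so a participant who declares smoking can still count as a sustained abstainer

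*Protocol article*

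**What the plan says.** - **Data Collection Variables** gives the classification rule: "A participant is identified as a nonsmoker when their CO levels measured by co-oximetry are below 10 ppm". It attaches no self-report condition.
- **Specific Outcomes Efficacy** determines the sustained abstinence rate in each arm "at 6 and 12 months, based on carbon monoxide co-oximetry results in ppm". Self-report enters in the next sentence, where the correlation between the CO-based rate "and the self-reported abstinence at 6 and 12 months will be calculated". Weekly point abstinence is also "based on the results obtained in the CO tests".
- **Limitations** says "Abstinence outcomes are objectively determined during in-person visits using co-oximetry". It then answers concern about the accuracy of CO monitors by saying that "combining this measurement with patient self-reporting improves the predictive capacity of co-oximetry".
- **Schedule of Participants, Table 3** records a participant statement at all 14 visits. Co-oximetry is recorded at the nine in-person visits: days 1, 7, 21, 90, 120 and 150, and weeks 24, 48 and 52. The telephone contacts on days 14, 25, 50 and 75 and at week 36 have a statement and no CO; the day-25 column, for example, is headed "Visit 5 (day 25; telephone)".
- **Efficacy Analysis** says that the dichotomous efficacy variable will come from an algorithm to be built once all study data are in.

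No section says that a declared lapse or relapse overrides a CO reading below 10 ppm.

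**The concern.** CO is a reading at one moment, and the trial also asks each participant at every contact whether they are smoking. The outcome text uses the first and sets the second aside. Two kinds of participant can then be counted as abstinent against their own declaration:

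1. Someone who says at an in-person visit that they smoke, but reads below 10 ppm.
2. Someone who reports relapse at a telephone contact and reads below 10 ppm at the in-person visits that follow.

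The second case has room to occur. No CO is taken between day 21 and day 90, or between week 24 and week 48. The Introduction reports that 20% of smokers on the 25-day regimen resumed smoking between the end of treatment and 2 months of follow-up. For the control arm that is roughly days 25 to 85, inside the first gap.

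At stake is the main efficacy outcome, with the relapse and interval-abstinence outcomes that share its definition and the economic analysis that uses the efficacy rate.

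**Working it through.** **1. The sections side by side**

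| Question | Data Collection Variables; Specific Outcomes Efficacy | Limitations |
|---|---|---|
| What makes a participant abstinent? | CO below 10 ppm | CO at in-person visits, said to be improved by combining it with self-report |
| Role of self-report | Separate variable, correlated with the CO-based rate | Part of a combined measure |
| Declared relapse with low CO | Meets the stated criterion | Not stated |

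A variable that is to be correlated with an outcome is not a component of that outcome. The safeguard claimed in Limitations is therefore absent from the outcome text.

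**2. The plan's own sample size**

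Inputs from Sample Size Determination: 30% in the control arm, 45% (0.40 in the bracket) in the 50-day arm, 50% in the 75-day arm, 80% power, 5% significance, 110 per arm, 21% losses, N = 402.

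- A three-group chi-square test (2 df) with 0.30/0.45/0.50 needs 109 per arm, against 110 stated. With 0.30/0.40/0.50 it needs 116.
- 110 × 1.21 = 133.1, rounded up to 134; 3 × 134 = 402.

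The planned figures are reproduced with 45%. The point here does not depend on them.

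**3. Illustration of the effect**

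Assumption: a share m of true non-abstainers is counted as abstinent. The documents give no value for m.

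Observed rate = p + m(1 − p). With equal m in both arms, the observed difference for 30% v 50% is 0.20 × (1 − m).

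Power, two-sided 5%, n = 110 per arm: Φ[(d − 1.96 × s0)/s1], with s0 = √(2 p̄(1 − p̄)/n) and s1 = √((p1(1 − p1) + p2(1 − p2))/n).

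At m = 0: d = 0.20, s0 = 0.0661, s1 = 0.0647, so power = Φ[(0.20 − 0.1295)/0.0647] = Φ(1.09) = 0.86.

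| m in control | m in 75-day arm | Observed rates | Difference | RR | Power |
|---|---|---|---|---|---|
| 0 | 0 | 30.0% v 50.0% | 20.0 points | 1.67 | 0.86 |
| 5% | 5% | 33.5% v 52.5% | 19.0 points | 1.57 | 0.82 |
| 10% | 10% | 37.0% v 55.0% | 18.0 points | 1.49 | 0.77 |
| 5% | 10% | 33.5% v 55.0% | 21.5 points | 1.64 | 0.90 |
| 10% | 5% | 37.0% v 52.5% | 15.5 points | 1.42 | 0.64 |

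Equal misclassification dilutes both the difference and the relative risk. In the unequal rows the difference can widen or narrow.

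**4. Why m is not a single-reading rate**

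Someone who relapses after day 25 and keeps smoking meets four CO tests by week 24 (days 90, 120 and 150, and week 24). If a smoker had an assumed 30% chance of reading below 10 ppm at one visit, the chance of passing all four would lie between 0.30⁴ = 0.8% (independent readings) and 30% (fully correlated readings).

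**The case against.** The strongest reply is that the protocol does not plainly adopt a CO-only outcome. The 10 ppm sentence stands in a list of tests and may be no more than the cut-off for one of them. The sentence before it describes co-oximetry as confirming abstinence, which can be read as confirming what the participant has said. Table 3 lists co-oximetry and the statement together under efficacy. Abstinence from day 25 to 50 and from day 25 to 75 can come only from telephone statements, since no CO is taken on those days. Efficacy Analysis leaves the algorithm open.

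This stands in part. A reader might infer that declared smokers will certainly be counted as abstinent. The documents support only that they can be, because self-report might still enter the algorithm. That does not rescue the rule: self-report would then enter by a choice made after all data are in, in an open-label trial. That the interval outcomes depend on statements shows that the outcome text is inconsistent.

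Other stronger readings also go too far:

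- *That the trial is biased toward no effect by a known amount.* Dilution requires equal misclassification across arms, and m has no source in the documents. It is also applied here to all non-abstainers, although participants lost to follow-up have no reading.
- *That CO misses all control-arm relapse.* Anyone still smoking has to pass the four tests from day 90 to week 24.
- *That the fix recovers all the lost power.* Smokers who deny smoking and read below 10 ppm pass under either rule.
- *That e-cigarette or other non-combusted nicotine use must count against abstinence.* That is a definitional choice, and the content of the statement item is not shown.

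**Conclusion.** The point holds as a conflict in the outcome definition. Two sections define abstinence by CO below 10 ppm with self-report outside the definition, a third relies on combining them, and nothing says how a declared relapse with a low CO is counted. Followed as written, the text allows declared smokers to be counted as sustained abstainers. This conclusion needs no value for m.

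The size cannot be derived from the documents. Under equal misclassification of an assumed 5% to 10% of non-abstainers, power for 30% v 50% at 110 per arm falls from about 86% to between 82% and 77%, and the relative risk from 1.67 to between 1.57 and 1.49. At 5% the power of this comparison stays above the planned 80%. With unequal shares the illustrated power runs from 64% to 90%. These figures show direction and rough scale and are not estimates of the loss in this trial.

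**What to change.** Reconcile Specific Outcomes Efficacy, Data Collection Variables and Limitations before any outcome data are seen, and carry the same rule into the algorithm named in Efficacy Analysis:

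- **Abstinent at a CO-tested visit:** the participant states no smoking and CO is below 10 ppm.
- **Sustained abstinence to 6 or 12 months:** no declared smoking at any contact after the quit date, telephone contacts included, and CO below 10 ppm at each in-person visit after the quit date up to the time point.
- **Declared relapse:** not abstinent, whatever the CO.
- **CO against self-report:** keep as a descriptive agreement table.

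The words *after the quit date* are needed. Visit 1 is on day 1 and records both measures, while the quit date may be as late as day 5. A rule covering every visit would fail participants for smoking before they were due to stop.

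The cost is a change of wording, with no added visit or CO test, since Table 3 already collects both measures. The Results section describes preselected participants who had not yet begun the initial visit, so at the time of writing the change could precede outcome data. The downside is somewhat lower abstinence rates in all arms.
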